### Analysis populations

#### Per-protocol (PP) population

This analysis population includes enrolled subjects who met all inclusion/exclusion criteria, complied with study treatment, and had RPR test results at the 6-month visit. To be compliant with study treatment, a subject must be able to swallow the pills and not vomit within 30 minutes of administration. No more than two consecutive missed doses will be considered as compliant with study treatment. Completion of at least 7 days of treatment or at least 14 capsules of 400 mg of cefixime will be considered as study compliant.

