### Primary objective

The primary objective of the study is to demonstrate the efficacy, as measured by a 4-fold (or more) decrease in rapid plasma reagin (RPR) titer from baseline to 6 months after treatment, with cefixime 400 mg taken orally two times a day for 10 consecutive days.

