### Efficacy and other analysis plan

#### Study population and follow-up status

The number of participants screened, eligible, randomized and with follow-up status (lost-to-follow-up, withdrawn or completed study follow-up) will be tracked, as well as the numbers analyzed in the per-protocol or by intention-to-treat population, by allocated arm.
Baseline characteristics of the study population will be summarized by allocated armFollow-up status at 3, 6 and 9 months showing the number of participants who came back for the visit will be tabulated by allocation armTabulated summary showing treatment adherence to cefixime and description of those who received the rescue therapy with BPG will be presented. Treatment adherence to cefixime is defined as patients taking all doses of cefixime or at least 14 doses without more than two consecutive missed doses.

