### Study outcomes evaluation

#### Primary analysis

The primary outcome is the proportion cured using cefixime treatment, evaluated at six months post-recruitment.

Proportion representing proportion cured using cefixime treatment success, cure defined as at least 4-fold reduction in RPR titer by six months (compared to baseline). Participants experience a 4-fold reduction in RPR before six months will be counted as a success at six months.

The primary analysis will assess whether the proportion cured is greater than or equal to 90% and whether the observed efficacy is statistically different than the minimally acceptable efficacy set at 80%. Proportion cured and 95% confidence intervals will be calculated using the binomial exact test. Cefixime will be declared efficacious if the lower limit for a two-sided 95% confidence interval (CI)≥ 0.80.
*Cure:* At least a 4-fold decrease in RPR from baseline to 6 months.*Failure:* Less than a 4-fold decrease in RPR titer from baseline to 6 months, or an increase in RPR titer.*Non-evaluable:* At least one of the following: Subject did not return for 6 month visit, or RPR results from the 6 month visit were not available for any reason, or subject could not be evaluated for any other reason.

For the PP analysis population, subjects with non-evaluable outcome status will be excluded from the analysis. For the ITT analysis population, subjects with non-evaluable outcome status will be included in analyses and classified as treatment failures. Subjects who discontinued early from the study due to a lack of treatment effect are included in all analysis populations as treatment failures.

The primary efficacy analysis will be based on the cure rate by 6 months and will be performed in the PP analysis population. The primary analysis will also be performed in the ITT population, but this is a secondary outcome measure.

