#### Secondary analysis

Secondary outcome measures will include the safety and tolerability of the study drug. These end points will be assessed among all subjects who have taken at least one dose of trial medication (including subjects who vomit within 1 hour of study drug administration).

The number of safety events* as measured by side effects and adverse events as well as tolerability reported by participants will be evaluated. The safety events will be tabulated by treatment allocation, event grade, severity and relatedness to study treatment [35]. The tolerability will be defined as the ability of participants to ingest all or at least 7-days or 14 doses of cefixime without experiencing treatment-related side effects or adverse events that cause the patient to discontinue the medication or that prevent the participant’s ability to complete the full course of treatment. The number of participants discontinuing therapy due to intolerance of cefixime will be reported.

**The types of safety events as collected on the side effects and adverse reporting questionnaires will be based on the period of medication administration (10 days) and at 14 and 30 days following the first dose of treatment.*

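### The per-protocol definition gives conflicting rules for a woman who vomits one dose: one sentence excludes her from the primary set, while another, and the separate adherence definition, count her as compliant.

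*Protocol article*

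**What the plan says.** All references are to the protocol article.

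- **Regimen** (Primary objective): "cefixime 400 mg taken orally two times a day for 10 consecutive days".
- **Vomiting condition** (Per-protocol (PP) population): to be compliant, "a subject must be able to swallow the pills and not vomit within 30 minutes of administration". The section does not say how many episodes matter, which dose is meant, or how a vomited dose is counted.
- **Missed-dose limit** (same section): "No more than two consecutive missed doses will be considered as compliant with study treatment".
- **Minimum exposure** (same section): "Completion of at least 7 days of treatment or at least 14 capsules of 400 mg of cefixime will be considered as study compliant".
- **Adherence to cefixime** (Study population and follow-up status): all doses, or "at least 14 doses without more than two consecutive missed doses". Vomiting is not mentioned.
- **Use of the set** (Primary analysis): "The primary efficacy analysis will be based on the cure rate by 6 months and will be performed in the PP analysis population". The intention-to-treat (ITT) analysis is also run, as a secondary measure.

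**The concern.** A per-protocol compliance rule should separate women who received adequate treatment from those who did not. Here two kinds of criterion stand in one definition with no rule for which prevails. One is a condition on vomiting, of a kind that suits a single-dose regimen. The other is a count of doses over a multi-dose course. They disagree about a woman who vomits once and otherwise takes everything.

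This matters because the definition decides who enters the primary test, in which cefixime is declared efficacious if the lower 95% confidence limit is at least 0.80. The trial is open label. Only the first cefixime dose is taken under direct observation, and later doses are followed by daily calls and text messages. If the condition covers every dose, it rests largely on self-report. An unresolved rule also leaves room to settle a woman's membership after her titre result is known. In addition, tolerability is itself a secondary outcome, so a literal application would condition the primary set on another outcome of treatment.

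**Working it through.** **1. Dose counts.**
- Planned: 2 per day × 10 days = 20 doses.
- Required: 14, so 20 − 14 = 6 may be missed; 14/20 = 70%.
- One dose vomited, all others kept: 19/20 = 95%.

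**2. The same two women under each rule.**

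| Rule | Woman A: 20 taken, one vomited within 30 minutes | Woman B: 14 taken, no run of three misses |
|---|---|---|
| PP: vomiting condition | not compliant | compliant |
| PP: at most two consecutive misses | compliant | compliant |
| PP: 14 capsules or 7 days | compliant | compliant |
| Adherence definition | adherent | adherent |

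Woman B's qualifier matters. There are 38,760 ways to miss 6 of 20 doses, and 28,665 of them (74%) contain no run of three or more. Six misses are accepted only in those patterns.

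**3. Does another reading remove the conflict?**
- *Any dose:* woman A is excluded with 95% exposure, and woman B is kept with 70%.
- *Observed first dose only:* a woman who vomits that dose and keeps the other 19 is still excluded, and woman B is still kept.
- *The 14-capsule sentence prevails:* woman A is kept, but the vomiting condition then has no effect for anyone who reaches 14 capsules.

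Every reading either ranks exposure the wrong way round or leaves one sentence without effect.

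**4. Number of women affected.** The adverse reactions listed under Potential risks include nausea (7%) but no vomiting rate, so the number cannot be computed. Allowing for the planned 20% loss, 140 × 0.80 = 112 evaluable women are expected. If 1% to 10% of them (an assumption) vomited a dose within 30 minutes, the set would fall to 112 × 0.99 ≈ 111 or 112 × 0.90 ≈ 101.

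**5. Shift in the estimate.** Let q be the share removed and c their cure rate, with 0.90 in the rest. The rate with them kept is (1 − q) × 0.90 + q × c, against 0.900 with them removed.

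| q | c = 0.70 | c = 0.80 | c = 0.90 |
|---|---|---|---|
| 2% | 0.896 | 0.898 | 0.900 |
| 5% | 0.890 | 0.895 | 0.900 |
| 7% | 0.886 | 0.893 | 0.900 |

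At 5% or less the shift is at most one percentage point. At 7% and c = 0.70 it is 1.4 points.

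**6. The plan's sample size.** With p0 = 0.80, p = 0.90 and an upper-tail level of 0.025, the smallest n with at least 80% power is 107 (94 or more cures; exact level 0.0233; power 0.819), and 107/0.80 gives 134. The stated 107 and 134 reproduce and do not depend on the vomiting rule.

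**The case against.** The best defence is that the text never states that one vomited dose in twenty disqualifies a woman. The 30-minute window matches the clinic observation after the supervised first dose, and the sentence "at least 14 capsules of 400 mg of cefixime will be considered as study compliant" can be read as covering a woman with 19 retained doses. This stands as far as it goes: exclusion of every woman who vomits once is something a reader might infer, not a settled rule. It does not remove the conflict, because the first-dose reading produces the same contradiction.

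A second defence is that the ITT analysis keeps these women and that tolerability is reported separately. Both are true, but ITT is secondary and does not settle who belongs in the primary set. A third is that counting rules for vomited doses often sit in a full protocol or analysis plan that is not shown. That would excuse silence. Here the article itself states the definition, and states it inconsistently.

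Two stronger readings are tempting and should not be made:

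- *A loss of power.* One could set 0.819 at n = 107 against 0.761 at n = 104. Exact binomial power is saw-toothed: it is 0.792 at 101, 0.801 at 109 and 0.772 at 112. Going from 112 to 109 women raises it. The drop is an artefact of the starting point, and the 20% allowance also covers factors other than dropout, which may include PP exclusions.
- *Two competing vomiting windows.* The Secondary analysis section has the phrase "including subjects who vomit within 1 hour of study drug administration". It only makes clear that every woman who took a dose is in the safety set. It needs no separate cut-off and does not contradict the PP rule.

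**Conclusion.** The concern holds as an internal contradiction in the definition of the primary analysis set. One vomited dose can exclude a woman with 95% of her course while a woman with 70% and no run of three misses is kept, and the adherence table can classify the first woman differently from the PP set. This rests on the wording and on the 20-dose count alone.

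The size is unknown and probably small. It is one percentage point or less if no more than 5% of women are removed and their cure rate is at least 0.70, against 0.90 in the others. These rates are assumptions. The documents do not support saying that the rule will in fact drop well-exposed women in any number because of a drug effect: no vomiting rate is given, and the condition can be read more than one way. The reason to act is that membership of the primary set should be fixed by one rule before outcomes are known.

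**What to change.** In the PP definition, replace the vomiting condition with a counting rule: a dose vomited within 30 minutes of administration counts as a missed dose. Apply the existing limits (at least 14 doses, no more than two consecutive misses) to the doses retained. Use the same definition for adherence under Study population and follow-up status. Continue to report vomiting under tolerability.

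The rewrite should also say that the two limits apply together, as the adherence definition already has it. As the PP text stands, a woman who stops after seven full days meets the seven-day criterion but has six consecutive missed doses.

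The cost is about one sentence and one coding rule on the adherence form; the daily calls already record adherence and side effects. Dosing and care do not change. The small downside is that a few women with one or two vomited doses enter the PP set, with exposure at or above the limit the plan already accepts.

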#### Intent-to-treat (ITT) population

This analysis population includes all enrolled subjects. We will conduct daily phone calls to the study participants to ensure adherence to study medications. Study participants will receive reminder texts to take their medication for the evening dose of medication. We will give reminder calls to patients prior to their scheduled follow up visits.

### Baseline characteristics

Baseline and demographic characteristics will be summarized. For both continuous and categorical variables, appropriate summary statistics will be applied. For continuous variables, descriptive statistics will include the number of non-missing values, mean, and standard deviation, median, minimum, and maximum. For categorical variables, descriptive statistics will include counts and percentages per category.

### Efficacy and other analysis plan

#### Study population and follow-up status

The number of participants screened, eligible, randomized and with follow-up status (lost-to-follow-up, withdrawn or completed study follow-up) will be tracked, as well as the numbers analyzed in the per-protocol or by intention-to-treat population, by allocated arm.
Baseline characteristics of the study population will be summarized by allocated armFollow-up status at 3, 6 and 9 months showing the number of participants who came back for the visit will be tabulated by allocation armTabulated summary showing treatment adherence to cefixime and description of those who received the rescue therapy with BPG will be presented. Treatment adherence to cefixime is defined as patients taking all doses of cefixime or at least 14 doses without more than two consecutive missed doses.

### Study outcomes evaluation

#### Primary analysis

The primary outcome is the proportion cured using cefixime treatment, evaluated at six months post-recruitment.

Proportion representing proportion cured using cefixime treatment success, cure defined as at least 4-fold reduction in RPR titer by six months (compared to baseline). Participants experience a 4-fold reduction in RPR before six months will be counted as a success at six months.

The primary analysis will assess whether the proportion cured is greater than or equal to 90% and whether the observed efficacy is statistically different than the minimally acceptable efficacy set at 80%. Proportion cured and 95% confidence intervals will be calculated using the binomial exact test. Cefixime will be declared efficacious if the lower limit for a two-sided 95% confidence interval (CI)≥ 0.80.
*Cure:* At least a 4-fold decrease in RPR from baseline to 6 months.*Failure:* Less than a 4-fold decrease in RPR titer from baseline to 6 months, or an increase in RPR titer.*Non-evaluable:* At least one of the following: Subject did not return for 6 month visit, or RPR results from the 6 month visit were not available for any reason, or subject could not be evaluated for any other reason.

For the PP analysis population, subjects with non-evaluable outcome status will be excluded from the analysis. For the ITT analysis population, subjects with non-evaluable outcome status will be included in analyses and classified as treatment failures. Subjects who discontinued early from the study due to a lack of treatment effect are included in all analysis populations as treatment failures.

The primary efficacy analysis will be based on the cure rate by 6 months and will be performed in the PP analysis population. The primary analysis will also be performed in the ITT population, but this is a secondary outcome measure.

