#### Study Visit 4 at six months following enrolment (allowable 44 days before or 45 days after scheduled visit):

Subjects that received either cefixime or BPG will be asked questions regarding their current symptoms, interval sexual history, concomitant antibiotic use and possible adverse reactions if they received cefixime. Subjects will have a venipuncture blood specimen collected for syphilis testing (RPR) increase in RPR titer at 3 or 6 months post treatment. Those subjects who experience a fourfold (two titer) increase in RPR titer at three or six months post treatment will be considered a treatment failure and will receive BPG 2.4 million units IM once per week three weeks. Data for these patients through Study Visit 4 will be included in analyses, and for analysis purposes, these patients will be considered to be treatment failures. All participants will undergo pregnancy testing. Those that are found positive on pregnancy testing will be treated for syphilis according to national guidelines and removed from the study. A voluntary repeat HIV test will be performed at 6 months. Patients that test positive for HIV at 6 months will be referred for HIV care. No additional treatment for syphilis will be provided based on HIV-positive status other than according to the study protocol. Response to treatment of these patients will be included in the analysis. Subjects that received either cefixime or BPG will be asked to return at 9 months from the time of treatment.

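### A woman with a 4-fold RPR fall at month 3 and no month-6 RPR is scored both as a success and as non-evaluable, and no order of precedence is given

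*Protocol article*

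**What the plan says.** The Primary analysis section sets the endpoint as "cure defined as at least 4-fold reduction in RPR titer by six months (compared to baseline" and adds that "Participants experience a 4-fold reduction in RPR before six months will be counted as a success at six months". Neither statement depends on a month-6 result.

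The same section defines non-evaluable to include "Subject did not return for 6 month visit, or RPR results from the 6 month visit were not available for any reason". It makes no exception for a woman who has already met the endpoint. Two consequences follow:

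- PP: "For the PP analysis population, subjects with non-evaluable outcome status will be excluded from the analysis".
- ITT: "subjects with non-evaluable outcome status will be included in analyses and classified as treatment failures".

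The Per-protocol (PP) population section separately requires that a woman "complied with study treatment, and had RPR test results at the 6-month visit". The note under Primary outcome measure points the other way: it keeps a month-3 decline as a success at three months even when the titer later rises.

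On the failure side, Study Visit 4 says of women with a 4-fold rise at month 3 or 6 that "for analysis purposes, these patients will be considered to be treatment failures". The Primary analysis section keeps women who stopped early for want of treatment effect in every population as failures.

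**The concern.** The section gives two scores for one record and does not say which prevails. The protocol's own schedule produces such records. RPR is drawn from every participant at month 3. Some women will be lost between months 3 and 6, and women found pregnant at month 3 are removed from the study.

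In ITT nothing else in the document settles the conflict. A literal reader counts as a failure a woman whose cure, as the endpoint is defined, was already recorded. In PP the membership rule points to exclusion, but the success sentence is unqualified and sits inside the definition of the primary outcome. A women-level scoring program written from that sentence alone would add early responders and no one else. What is at stake is a clear ITT estimate and protection of the PP decision from that misreading. The point concerns only women without a month-6 RPR. How a relapse seen at month 6 is scored is a separate question.

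**Working it through.** **1. The plan's own figure.** Inputs from Sample size considerations and Primary analysis: p0 = 0.80, p = 0.90, exact two-sided 95% interval, success if the lower limit is at least 0.80. For n = 107 the smallest count whose Clopper–Pearson lower limit reaches 0.80 is 94. P(X ≥ 94 | 0.80) = 0.0233 and P(X ≥ 94 | 0.90) = 0.819. Inflation: 107 / 0.80 = 133.75, so 134; the plan enrols 140. The design reproduces.

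**2. Three records, all with baseline 1:64 and no month-6 RPR.**

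| Month 3 | Success or failure wording | Non-evaluable wording |
|---|---|---|
| A: 1:16 (4-fold fall) | Success | Out of PP; ITT failure |
| B: 1:32 (2-fold fall) | Neither met | Out of PP; ITT failure |
| C: 1:256 (4-fold rise) | Failure (Study Visit 4) | Out of PP; ITT failure |

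A is contradictory in both populations. B is consistent. C is a failure in ITT either way. In PP she is out, unless loss after a month-3 rise counts as stopping for want of effect, which the text does not say.

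**3. Assumptions for size.** The documents give no month-3 response rate and no timing of loss. Let L be the share without a month-6 RPR, a the share of those seen at month 3, and f the share of these with a 4-fold fall. Base case: L = 0.20 (the plan's whole dropout allowance), a = 0.50, f = 0.60 to 0.70. That is 140 × 0.20 = 28 women without month 6, and 28 × 0.50 × 0.60 to 0.70 = 8 to 10 early responders. Missingness is taken as unrelated to outcome.

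**4. ITT.** At a true cure rate of 0.90:

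- Literal rule: 0.80 × 0.90 = 72%.
- Crediting observed falls: add L × a × f = 0.20 × 0.50 × 0.60 = 6 points, or 7 points at f = 0.70, giving 78% to 79%.
- With a from 0.25 to 0.75 the shift runs from 0.20 × 0.25 × 0.60 = 3 points to 0.20 × 0.75 × 0.70 = 10.5 points.

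**5. PP, only if the success sentence overrides the membership rule.** M ~ Bin(140, L) women lack month 6; n = 140 − M; X ~ Bin(n, p) cures; S ~ Bin(M, a × f) early responders. With r(n) the smallest passing count, the literal rule passes if X ≥ r(n) and the override passes if X + S ≥ r(n + S). Summing the binomial probabilities:

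| True cure | L | a | f | Literal | Override |
|---|---|---|---|---|---|
| 0.80 | 0.20 | 0.50 | 0.60–0.70 | 1.8% | 4.4–5.0% |
| 0.80 | 0.20 | 0.25–0.75 | 0.60–0.70 | 1.8% | 2.9–7.6% |
| 0.80 | 0.10 | 0.50 | 0.60–0.70 | 1.9% | about 3% |
| 0.80 | 0.05 | 0.50 | 0.60–0.70 | 1.9% | about 2.4% |
| 0.85 | 0.20 | 0.50 | 0.65 | 23% | 37% |

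The nominal upper tail is 2.5%. In the last row the two readings disagree in 14% of trials. As an example, 97/112 has lower limit 0.789 (not efficacious), while adding 10 early responders gives 107/122 with lower limit 0.805 (efficacious).

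**6. Month-3 failures kept in PP without a month-6 RPR.** In the same model at p = 0.90 and L = 0.20, power is 0.81 with none, 0.73 with one such woman and 0.64 with two.

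**The case against.** The strongest reply is that PP is already settled. Membership requires a month-6 RPR, and the Primary analysis section repeats the exclusion of non-evaluable women. The success sentence scores outcomes and says nothing about who belongs to an analysis set. This stands. A reader might infer that the plan itself lets early responders into PP one-sidedly, or that two analysts following it faithfully could reach opposite efficacy conclusions. The documents do not support that: one of the two would have to disregard two stated exclusions. The figures in step 5 measure the cost of that misreading.

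A second reply is that the ITT rule is explicit and conservative, and that ITT is secondary with no decision of its own. This stands in part. At the base-case rates the chance of reaching the 122/140 needed for a lower limit of 0.80 is well under 0.01% at 72% and about 0.6% at 78.5%, so the 0.80 criterion would almost never be met in ITT either way. But missing-as-failure is a convention for unobserved outcomes, and here the defined outcome was observed.

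A third reply is that the 20% allowance also covers other factors, and that the month-6 window is wide. This also stands, which is why the 10% and 5% rows are shown.

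**Conclusion.** The contradiction is real, lies within one section, and is not resolved for ITT anywhere in the document. It is not a detail left to an analysis plan, because both rules are stated and they disagree.

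Its firm consequence is confined to a secondary analysis: about 6 to 7 points on the ITT cure proportion, resting on the assumed 20% loss, 50% month-3 attendance and 60–70% early response. For the primary PP decision the literal text gives exclusion, and with missingness unrelated to outcome that reading is unbiased. The rise in false-positive risk to 4.4–5.0%, or about 3% with 10% missing, is conditional on overriding that text.

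There is a smaller loose end in the other direction. Women who stop for want of effect stay in PP as failures, while early responders without month 6 leave it, and a woman with a month-3 rise who is then lost has no clear place.

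**What to change.** Three changes of wording:

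1. In Primary analysis, state that the success sentence for falls before six months admits no one to PP. A month-6 RPR is required there whatever the month-3 result, in line with the PP population section.
2. In ITT, where the denominator is fixed, count a 4-fold fall observed before month 6 as meeting the endpoint. Classify as non-evaluable failures only women with no observed 4-fold fall and no month-6 RPR. Keep the version that scores every missing month-6 result as failure as a sensitivity analysis.
3. Reconcile Study Visit 4 and the want-of-effect clause with the PP membership rule for women with a 4-fold rise at month 3 and no month-6 RPR. If they stay in PP as failures, say that this is a deliberate conservative exception. It is outcome-dependent entry that lowers the PP cure rate and the power, as step 6 of the working shows.

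The cost is a few sentences and an ITT estimate that is slightly less conservative. Month-3 RPR is already collected, so no new data are needed.

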### Outcome measures

#### Primary outcome measure

The primary study outcome will be based on the change in the RPR titer from baseline to six months. Those subjects who have a 4-fold decrease in RPR titers from baseline by six months will be considered a positive treatment response (treatment success). All other participant outcomes will be defined as treatment failure including those subjects who experienced a fourfold (two titer) increase in RPR titer at three or six months post treatment and received BPG 2.4 million units IM once per week for 3 weeks.

**Note:** Subjects that received either cefixime or BPG that experience a 4-fold titer decline by three or months followed by a 4-fold titer rise by six or nine months will be classified as (1) treatment success at three months and (2) syphilis re-infection during the period following the initial 4-fold RPR titer decline.

**Note:** While there are limited data on the use of cefixime for the treatment of syphilis, cefixime is a broad spectrum, third generation cephalosporin in the same class and family as ceftriaxone for which extensive data on treatment efficacy for syphilis are available. RPR titers will be monitored frequently in this study and treatment with BPG will be provided if RPR titer increases fourfold (2 titer) at 3 or 6 months or does not reflect an adequate response (fourfold or 2-titer decline) at 6 months.

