### Sample size considerations

The primary analysis will compute the proportion of subjects with a 4-fold decrease (from study entry RPR) in RPR titers from baseline by six months in the per-protocol (PP) analysis population.

We have powered this study to detect a significant difference from a minimal accepted efficacy of standard treatment with benzathine penicillin (80%). This minimal efficacy was selected based on a multi-center clinical trial evaluating the efficacy of penicillin versus azithromycin [36].

A 90% response rate for cefixime was selected based on recent meta-analyses, a multi-center trial of ceftriaxone for treatment of syphilis [10, 11, 37, 38]. To calculate the number of subjects required to enroll to reach 94 evaluable subjects in the PP analysis population, the following assumptions are made:

Using a two-sided exact binomial test at α = 5%, a sample size of 107 achieves an 80% power to detect a minimum acceptable cefixime efficacy (p_0_) of 0.80, assuming the anticipated efficacy proportion (p) of 0.90. Assuming 20% dropout rate and other related factors, the final sample size for the cefixime arm is inflated to *N* = 140, with correspondingly 70 participants recruited in the BPG arm, in a ratio (cefixime to BPG) of 2:1 (Table 4).

**Table 4 Tab4:** Sample size to detect a minimum acceptable efficacy (p_0_) of 0.80 using a two-sided Exact binomial test for difference assuming alpha = 5% and power = 80%*

Anticipated efficacy *P*	Sample size *	Effective sample size (20% inflated) *n*
0.86	316	395
0.87	225	282
0.88	173	217
0.89	131	164
0.90	107	**134**
0.91	88	110
0.92	69	87
0.93	55	69
0.94	48	60
0.95	41	52
0.96	34	43
0.97	26	33
0.98	26	33
0.99	17	22

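### The rules for the primary endpoint contradict each other: the same titre sequence can be both cure and failure, and the protocol does not say which rule prevails

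*Protocol article*

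**What the plan says.** - **Primary analysis.** Cure is first described as a fall of at least four-fold *by* six months, and then: "Participants experience a 4-fold reduction in RPR before six months will be counted as a success at six months". The list that follows defines Cure by the change from baseline *to* month 6, and Failure as "Less than a 4-fold decrease in RPR titer from baseline to 6 months, or an increase in RPR titer". A woman without a month-6 visit or result is Non-evaluable: left out of the per-protocol analysis and counted as a failure under intention to treat. Cefixime is declared efficacious if the lower exact two-sided 95% limit reaches 0.80. The per-protocol population is primary.
- **Primary outcome measure.** Success is a four-fold fall by six months. Every other outcome is failure, "including those subjects who experienced a fourfold (two titer) increase in RPR titer at three or six months post treatment". The first Note says that women with a four-fold fall followed by a four-fold rise "will be classified as (1) treatment success at three months and (2) syphilis re-infection during the period following the initial 4-fold RPR titer decline".
- **Study Visit 4.** A four-fold rise at three or six months is again a treatment failure. Neither this section nor Primary outcome measure names the titre from which the rise is measured. Potential risks, under Ethical concerns, measures it from the entry RPR.
- **Other sections.** The Abstract, Main variables and Sample size considerations use *by* six months. The Primary objective uses *to* six months.

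**The concern.** A response *by* six months and a response *at* six months are different endpoints. They part company for any woman whose titre falls four-fold at month 3 and then climbs back. The protocol uses both, gives no order of precedence, and classifies such a woman in opposite ways.

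The efficacy decision is one proportion against a fixed 80% bar, and the BPG arm is not formally compared, so a shift in classification has nothing to offset it. At the planned size one woman decides the result: 94 cures of 107 pass and 93 fail. The trial is also open-label, so an unresolved choice between rules is best settled before the titres are analysed.

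**Working it through.** **1. The rules side by side.** Titres are baseline, month 3, month 6.

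| Sequence | Early-success sentence | Cure/Failure list | Note (fall, then rise) | Four-fold-rise rule |
|---|---|---|---|---|
| 1:64, 1:16, 1:32 | Success (64/16 = 4) | Failure (64/32 = 2) | Does not apply (32/16 = 2) | Does not apply |
| 1:32, 1:8, 1:128 | Success (32/8 = 4) | Failure (increase) | Success plus re-infection (128/8 = 16) | Failure, even from entry (128/32 = 4) |
| 1:64, 1:16, 1:64 | Success (64/16 = 4) | Failure (64/64 = 1) | Success plus re-infection (64/16 = 4) | Depends on reference: 64/64 = 1 from entry, 64/16 = 4 from month 3 |
| 1:64, 1:16, none | Success (64/16 = 4) | Non-evaluable | Does not apply | Does not apply |

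The first two rows are contradictions on any reading of the reference titre. In the third row, the four-fold-rise column turns on the reference titre. The fourth is an early responder with no month-6 RPR, whose class the two rules settle differently.

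**2. Direction.** Take women with a month-6 RPR, as the per-protocol population requires. Let p be the proportion with a four-fold fall still present at month 6, and q the proportion with an earlier four-fold fall no longer present. The *by* rate is p + q and the *at* rate is p. Since q cannot be negative, the early-success rule can only raise the rate relative to a month-6 definition.

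**3. The plan's own figure.** Sample size considerations states: "Using a two-sided exact binomial test at α = 5%, a sample size of 107 achieves an 80% power", for a "minimum acceptable cefixime efficacy (p_0_) of 0.80", "assuming the anticipated efficacy proportion (p) of 0.90". The bar r is the smallest count with P(X ≥ r | n, 0.80) ≤ 0.025.

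- n = 107: r = 94, upper tail 0.0233, power at 0.90 = 0.819. The Clopper-Pearson lower limit is 0.8012 at 94/107 and 0.7902 at 93/107.
- 107 / 0.8 = 133.75, rounded up to 134, as in Table 4. Enrolment is 140.
- 140 × 0.8 = 112 evaluable: r = 99, upper tail 0.0137.

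The stated 107 and 134 reproduce, so the sample size arithmetic is not at issue here.

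**4. Illustration of size.** The document gives no relapse or re-infection rate, so q is an assumption. With month-6 response truly p = 0.80, the chance of declaring efficacy under the early-success rule is P(X ≥ r | n, 0.80 + q).

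| Assumed q | n = 107, bar 94 | n = 112, bar 99 |
|---|---|---|
| 0% | 2.3% | 1.4% |
| 1% | 4.1% | 2.6% |
| 2% | 6.9% | 4.5% |
| 3% | 11.1% | 7.7% |
| 5% | 25.0% | 19.3% |

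At n = 107, 3% is about three women (107 × 0.03 = 3.2).

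**5. The opposite choice.** If 0.90 was meant as a *by* rate, the month-6 rate is 0.90 − q. Power at n = 107 under a month-6 definition is P(X ≥ 94 | 107, 0.90 − q): 81.9% at q = 0, 71.3% at 1%, 59.2% at 2%, 46.7% at 3% and 25.0% at 5%.

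**The case against.** The strongest defence is that the early-success rule is a deliberate, prespecified choice. *By* six months is the commoner wording, Primary analysis closes on the cure rate by six months, and the Note says explicitly how later rises are handled. On that view the Cure/Failure list is generic text that was never aligned. This makes *by* the likelier intention, but the Failure line and the four-fold-rise rule still say otherwise and would have to be corrected.

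A reader might infer that the rule inflates the cure rate tested against 80%. The document does not support that. It gives no frequency for transient response. If response by six months is the intended quantity, the error rate at a true 80% is still 2.3%. The protocol does not say whether the 80% benchmark is itself a *by* or an *at* rate. Where a later rise is true re-infection, counting the woman as a success does not overstate the drug's effect.

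A reader might also infer that relapses are knowingly counted as cures. Interval sexual history is recorded at months 3, 6 and 9, partners are referred, and the BPG arm is included partly to account for re-infection. What stands is narrower: no stated criterion uses these data to separate relapse from re-infection, so a relapse with a four-fold rise would carry the re-infection label.

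Finally, 1:64, 1:16, 1:64 might be offered as a failure under the four-fold-rise rule. That needs the rise to be taken from month 3, whereas the only stated reference is the entry RPR. The first two rows of the table do not depend on this.

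**Conclusion.** The contradiction is established from the text alone: Primary analysis conflicts with itself, and so does Primary outcome measure, where Study Visit 4 repeats the four-fold-rise rule. It affects the only efficacy endpoint and should be resolved.

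The direction is established among women with a month-6 RPR: the early-success rule gives a rate equal to or above the month-6 rate. The amount is unknown. The rise from 2.3% to between 4.1% and 25.0% at n = 107 rests on assumed shares of 1% to 5% and on treating response at month 6 as the quantity of interest. It shows how sensitive the decision is to a few women and is not an estimate of bias. Whether the endpoint should be *by* or *at* six months is a choice of estimand that the document leaves open to the sponsor.

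**What to change.** Before titres are analysed, and in a dated amendment because enrolment has begun:

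- State one primary definition, *by* or *at* six months, and use it in the Abstract, Primary outcome measure, Sample size considerations and Primary analysis. Align the Cure, Failure and Non-evaluable list with it.
- State the reference titre for a four-fold rise, so that Study Visit 4, Primary outcome measure and Potential risks agree.
- State which rule takes precedence when a fall is followed by a rise, and how a month-3 responder without a 6-month RPR is classed in each analysis population.
- Report the other definition as a prespecified sensitivity analysis against the same 80% bar, and list the women whose classification differs.

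The cost depends on the choice. Keeping *by* six months needs wording changes only, and the sensitivity analysis shows how far the result depends on transient responses. Choosing *at* six months counts true re-infections as failures and replaces the stated early-success rule after enrolment has started. If 0.90 was a *by* rate, it also lowers power from 81.9% to 59.2% or 46.7% when 2% or 3% of women lose their response. The amendment should state this.
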